### Diet intervention

If participants have a BMI > 27 kg/m^2^, are aged < 80 years and do not have specific conditions which are likely to require medical supervision to participate in a ketogenic VLED (type 1 diabetes, type 2 diabetes requiring medication apart from metformin, using warfarin, stroke or cardiac event in the previous 6 months, unstable arrhythmia, constipation requiring medical intervention in the past 12 months, restriction of fluid intake or renal problems with estimated glomerular filtration rate < 30 mL/min/1.73m^2^), they can also opt to have six individual videoconferencing consultations with a dietitian to undertake a dietary weight loss intervention [20, 21]. Participants must also be willing to undertake the VLED using the meal replacement products to be eligible for the dietitian consultations.

The initial dietitian consultation will be approximately 45 minutes in duration with follow-up consultations approximately 30 minutes. It is recommended that the six consultations occur in weeks 2, 4, 6, 9 to 12, 14 to 17 and 19 to 23 but the exact timing will be agreed between each participant and their dietitian. During the consultations, appropriate weight loss goals will be agreed and a tailored management plan for losing weight developed. Conversations based on motivational interviewing principles and techniques will be used to develop readiness to change (motivation) and confidence to self-manage. Ongoing education, information and advice are key components of the intervention to optimally support weight loss. The dietitian will use follow-up consultations to review progress, goals and weight loss progress and together with the participant make modifications as required. The dietitian will assist in providing behaviour change support and assistance to overcome obstacles to the participant enacting the agreed weight loss plans. Core behaviour change techniques employed by the dietitian are specified in Table 1.

The diet intervention comprises two phases:Intensive weight loss through a ketogenic VLED [35] for up to 16 weeks and aiming for ≥10% loss of body weight, as this is associated with clinically important improvements in knee OA pain and function [36, 37]. The ketogenic VLED involves replacing two meals, generally breakfast and lunch, with formulated meal replacement products (Optifast® meal replacements, or if unavailable or the participant is vegetarian, Optislim®) provided at no cost to the participant. These products provide most of the vitamins, minerals, and metals required for optimal nutrition, and come as soups, shakes and bars in various flavours. On the diet, one prepared meal (generally dinner) comprises protein (e.g. white or red meat, fish or seafood, eggs, or tofu) and non-starchy vegetables/salad. A small amount (i.e. 1 tablespoon) of fat/oil is also recommended for this meal to stimulate gallbladder contraction (if the gallbladder is in situ). In total, the diet contains approximately 800 cal (3280 kJ) per day and < 60 g of carbohydrates.Transition from ketogenic VLED onto a longer-term eating plan for weight maintenance. After 16 weeks (or earlier if the participant has reached their weight loss target), participants will be guided to progress to one meal replacement per day for a further 4 weeks (supplied at no cost to the participant) and to reintroduce foods containing carbohydrates, to aid the gradual transition to a weight maintenance phase. Participants will be advised to follow a healthy eating diet consistent with the principles of the Commonwealth Scientific and Industrial Research Organisation total wellbeing diet [38] (i.e. high protein, low glycaemic index carbohydrate, low fat). Participants are encouraged to continue to weigh themselves regularly (e.g. at least once per week) and to restart the ketogenic VLED taking meal replacements for 1 to 2 weeks if they regain 2 kgs or more. The dietitian will refer the participant to see their general practitioner for a health check if they lose > 20% of their body weight within 6 months, or for monitoring of known health problems if deemed necessary (e.g. hypertension).

#### Enabling and behaviour change strategies/resources (see Tables 1 and 2)

Participants will be provided with resources to facilitate the management plans the physiotherapists will deliver during the sessions. These resources include: a welcome letter describing their involvement in the study; hard copy information booklets; four coloured therabands (red, green, blue, and black) and an adjustable cuff weight (0.5 to 5 kg) for performing strengthening exercises; and a wearable activity tracker to monitor daily step count.

**Table 2 Tab2:** Summary of resources provided to participants in the *Better Hip* group^a^

Resource	Description	*Better Hip* program (eligible for weight loss intervention)	*Better Hip* program (not eligible for weight loss intervention)
Consultations with a physiotherapist	6 videoconferencing consultations over 6 months. Prescribes structured exercise and physical activity plan and behaviour change support	✓	✓
Consultations with a dietitian	6 videoconferencing consultations over 6 months. Supports participant to undertake ketogenic VLED, including behaviour change support	✓	
Exercise bands	4 exercise resistance bands (red, green, blue, black) for strengthening exercises	✓	✓
Exercise weights	Adjustable ankle cuff weight (0.5 kg – 5 kg) for strengthening exercises	✓	✓
Fitbit® activity tracker	Activity tracker used to track participants’ steps and physical activity	✓	✓
Access to My Exercise Messages mobile app	Mobile app which tracks weekly exercise sessions and provides personalised messages to help overcome obstacles to exercise	✓	✓
Digital weight scales	Provided to those who do not already have access to scales	✓	
VLED plastic portion plate	Assists with portion sizes (for use during the VLED phase of the dietary intervention)	✓	
Weight maintenance plastic portion plate	Assists with portion sizes (for use during the weight maintenance phase of the dietary intervention)	✓	
Optifast® meal replacements	Up to 6 months supply of meal replacements for the ketogenic VLED	✓	
Educational video about the VLED	Short video about the ketogenic VLED featuring endocrinologists and dietitian experts, and a person with OA	✓	
Booklets			
Preparing for your consultations	Details about consultations, instruction on how to use Coviu videoconferencing	✓	✓
Osteoarthritis information	Information about osteoarthritis, typical management options, weight loss, pain coping skills and sleep	✓	✓
Exercise booklet	Strengthening exercise instructions and photographs	✓	✓
Hip care plan and log book	Templates to record details of management plans and complete exercises	✓	✓
Weight management ‘how to’ guide	Describes the ketogenic VLED and provides information about healthy food choices and portion sizes	✓	
Weight management behavioural support activities	Workbook that contains information and templates to track weight, a food diary, tips to find a support person, identify food triggers, plans for ‘at risk’ scenarios, overcoming barriers, changing thought patterns, and monitoring hunger levels	✓	
Recipe book	Suitable recipes for ketogenic VLED	✓	
Food list pocket guide	Low carbohydrate ingredients to consume when on the ketogenic VLED	✓	

*VLED* Very low energy diet, *OA* Osteoarthritis.

^a^Adapted from: Bennell KL, Keating C, Lawford BJ, et al. Better Knee, Better Me™: effectiveness of two scalable health care interventions supporting self-management for knee osteoarthritis–protocol for a randomized controlled trial. BMC musculoskeletal disorders. 2020;21(1):1–19

Physiotherapists will advise the participants to download the ‘My Exercise Messages’ app [39] which we developed and which is freely available from the Apple Store or Google Play. ‘My Exercise Messages’ was created to help support people with OA stick to their weekly exercise goals, including exercise prescribed by health professionals. The app works by tracking weekly exercise sessions and providing personalised messages to help overcome obstacles to exercise, and was based on a Short Message Service (SMS) program which was proven to enhance exercise adherence in an OA population [40]. Physiotherapists will advise the participants to use the app to track performance of their strengthening exercise program.

Additional resources for those undertaking weight management include:A plastic “portion plate” to help manage meal portion sizes and stick to the ketogenic VLED when preparing meals;Another plastic “portion plate” to help manage meal portion sizes when transitioning to the healthy eating diet for weight maintenance;A set of digital weight scales for those who do not already have access to scales;Weight management ‘how to’ guide describing the ketogenic VLED, healthy food choices and portion sizes;Ketogenic recipe book;Food list pocket guide;Workbook with information and templates to track weight, a food diary, tips to find a support person, identifying food triggers, planning for “at risk” situations, overcoming barriers, changing thought patterns, and monitoring hunger levels.

Resources and strategies that the dietitian will use to provide behaviour change support include: setting realistic goals; keeping a food diary; monitoring weight regularly (at least weekly); finding a support person to help; learning about healthy food choices and portion size; identifying food triggers; planning for ‘at risk’ situations; working out barriers and finding ways to overcome them; changing any negative thought patterns; engaging in relaxation, mindfulness and distraction techniques; monitoring hunger levels before, during and after meals to help identify physical and psychological hungers and strategies to overcome psychological hunger.

### Web-based information (control)

This group will receive online information about hip OA and its management via a custom website accessible during their involvement in the study via password login. The Trial Coordinator will call participants allocated to the control group upon study enrolment to explain group allocation and how to access the website, after which the website URL and login details will be emailed to the participant. The website will include educational information about OA, recommended treatment options, exercise and physical activity, weight loss, managing pain, and optimising sleep, as well as links to external websites for further help and support (e.g. MyJointPain, painHEALTH, Musculoskeletal Australia).

### Outcome measures

Participant-reported outcomes will be collected online via REDCap data capture platform at baseline, 6 months and 12 months. All participants who complete the 12-month re-assessment will be given a $50 gift voucher as compensation for the considerable time they have invested in the trial. An online survey for follow-up of primary and secondary outcomes will also be conducted at 2 years post randomisation. These longer-term results will be reported separately to the main trial results and will occur after analysis of the main trial data.

Primary outcomes are reliable and valid measures recommended for use in clinical trials of hip OA [41]. These will be measured at baseline, 6 and 12 months, and include i) change in average severity of hip pain on walking in the past week measured on an 11-point NRS, where 0 = “no pain” and 10 = “worst pain possible”; ii) change in physical function subscale of the Western Ontario and McMaster Universities Osteoarthritis Index (WOMAC) [42] with scores from 0 to 68, where higher scores indicate greater dysfunction. Conclusions about effectiveness will be based on the 6 month time point change in the primary outcomes.

The secondary outcomes will be measured at baseline, 6 and 12 months unless otherwise indicated and include:i)Change in Hip dysfunction and Osteoarthritis Outcome Score (HOOS) [43] subscale of pain with normalised scores ranging from 0 to 100, with 100 indicating no symptoms;ii)Change in HOOS [43] subscale of hip-related quality of life, with normalised scores ranging from 0 to 100, with 100 indicating better quality of life;iii)Change in HOOS [43] subscale of function, sports and recreational activities with normalised scores ranging from 0 to 100, with 100 indicating better function;iv)Change in self-reported body weight measured in kilograms;v)Change in health-related quality of life using the Assessment of Quality of Life instrument (AQoL-8D) [44], a 35-item instrument with scores ranging from − 0.04 to 1.0, with higher scores indicating better quality of life;vi)Change in physical activity levels evaluated using the Physical Activity Scale for the Elderly (PASE) [45] with scores from 0 to 400, where higher scores indicate greater levels of physical activity;vii)Perceived global rating of overall change in hip condition scored on a 7-point Likert scale from ‘much worse’ to ‘much better’ [46] at 6 and 12 months. Participants who indicate that they are “moderately better” or “much better” will be categorised as ‘improved’;viii)Self-reported hip replacement procedures, where participants will be asked if they have had a hip joint replacement since their study enrolment on the study hip at 6 and 12 months;ix)Willingness to undergo hip replacement surgery self-rated using a 5-point Likert scale with anchors “definitely not willing” and “definitely willing”. Participants indicating ‘probably willing’ or ‘definitely willing’ will be classified as ‘willing’;x)Use of oral pain medications self-reported and defined as one or more of analgesics (paracetamol combinations) and/or oral non-steroidal anti-inflammatory drugs and/or oral glucocorticoids and/or oral opioids taken at least once a week in the prior month for hip pain.

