### Trial sample size

We aim to detect the minimal clinically important difference (MCID) over 6 months on the two primary outcomes of i) change in hip pain during walking (NRS) and ii) change in physical function (WOMAC). The MCID in OA trials is a 1.8-unit pain change [53] and 6-unit function change [42]. The sample size calculation accounts for potential clustering by physiotherapists in the *Better Hip* group. Based on our research [54], we assume a conservative between-participant standard deviation of 2 pain units and 11 function units, correlations between baseline and 6-month scores of 0.25 for pain and 0.4 for function, an intra-cluster correlation of 0.05 and 5 physiotherapists treating participants. With these parameters, we need 90 per group to achieve 80% power to detect the MCID in function at a 0.025 significance level (due to two primary outcomes). This gives > 99% power to detect the MCID in pain. Allowing for 15% attrition, we will recruit 106 people per group (in total *n* = 212).

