### Data analysis plan

We will use intention-to-treat analyses. For the two primary outcomes and other secondary continuous outcomes, mean differences in change over time between groups will be estimated via separate linear mixed-effects models, with random effects for participants and physiotherapist. Models will be adjusted for baseline outcomes and BMI (> 27 kg/m^2^ and ≤ 27 kg/m^2^). Terms for time and treatment will be included, and their interaction, and results reported as mean difference in outcomes at 6 months (primary timepoint) and at 12 months between the *Better Hip* group and control group. These models provide valid inference in the presence of missing data if the data are missing at random. An analysis will be conducted using the delta-adjustment method under the pattern-mixture modelling framework in the context of multiple imputation to assess sensitivity to missingness not at random. To aid clinical interpretation, the primary outcomes will also each be dichotomised into those who do and do not achieve the MCID in improvement in pain (1.8 NRS units) and function (6 WOMAC units). Counts and percentages of participants achieving the MCID in improvement in pain and function will be reported in each treatment group at 6 and 12 months. For binary outcomes (clinically-relevant improvement, global change, participants using any oral pain medication at least once per week, participants undergoing a hip replacement procedure, willingness to have hip replacement surgery), logistic mixed-effects models will be fitted adjusted for the outcomes at baseline where able and BMI (> 27 kg/m^2^ and ≤ 27 kg/m^2^), with random effects for participant and physiotherapist, and results reported as risk ratios and risk differences at 6 months between the treatment groups. Analysis of moderation of the treatment effect by pre-specified potential moderators (baseline willingness to have surgery, BMI) on the two primary outcomes will be assessed by including interactions between moderators and the treatment group in the regression models. For all between-group comparisons, 95% confidence intervals and *p*-values will be reported. Standard diagnostic plots will be used to verify model assumptions.

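### Global change has no baseline value, so its model adjusts for BMI stratum alone and forgoes a modest, nearly free gain in precision from baseline walking pain and function

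*Protocol article*

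**What the plan says.** **Timing.** The Outcome measures section sets a default: "The secondary outcomes will be measured at baseline, 6 and 12 months unless otherwise indicated". Global change is item vii of that list, "Perceived global rating of overall change in hip condition scored on a 7-point Likert scale". Its timing follows the scale description (the fragment opens with the end of a reference number): "46] at 6 and 12 months. Participants who indicate that they are". It is therefore an exception to the default and has no baseline value.

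**Model.** The Data analysis plan places it among the dichotomous endpoints: "For binary outcomes (clinically-relevant improvement, global change, participants using any oral pain medication at least once per week". The rule for these is that "logistic mixed-effects models will be fitted adjusted for the outcomes at baseline where able and BMI", followed by "with random effects for participant and physiotherapist, and results reported as risk ratios and risk differences at 6 months".

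**Baseline severity.** The primary outcomes are walking pain and WOMAC function: "These will be measured at baseline, 6 and 12 months, and include i) change in average severity of hip pain on walking". Each score adjusts its own linear model. Under Randomisation, blinding and allocation concealment, allocation is disclosed only once baseline assessment is complete. No section enters either score in the global-change model.

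**The concern.** The covariate rule allows for outcomes without a baseline measurement but names no substitute for them. For global change the first covariate is empty, so the model contains treatment, time as applicable, the BMI stratum and the random effects.

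A rating of how the hip has changed since the start may well depend on how bad the hip was at the start. If it does, baseline pain and function would explain part of its variation, and leaving them out makes the risk difference less precise than it could be. A second, smaller issue concerns missing ratings. A model conditioning only on treatment and BMI stratum needs dropout to be ignorable given those alone, whereas the pain and function models also condition on baseline severity. At stake are some precision and some robustness to dropout in one secondary outcome. The validity of the comparison is not in question.

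**Working it through.** **1. The plan's own figure.** The protocol states no sample size, power or precision for global change. The only planning figure is 90 analysable per group for WOMAC function (Trial sample size).
- Inputs: difference 6, SD 11, intra-cluster correlation 0.05, 5 physiotherapists, alpha 0.025 (taken as two-sided).
- Design effect in the Better Hip arm: 1 + (90/5 − 1) × 0.05 = 1.85.
- Standard error: 11 × √((1.85 + 1)/90) = 1.96.
- Power: Φ(6/1.96 − 2.24) ≈ 79.5%, or 92 per group for 80%.
- Attrition: 90/0.85 = 105.9, so 106 per group.

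The stated 90 is reproduced closely, with SD 11 used without a further reduction for the 0.4 correlation. I take 90 per group as the analysable size below.

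**2. Covariates left by the rule.** Own baseline value: none. BMI stratum: kept. Baseline walking pain and WOMAC function: not named.

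**3. Approximate gain.** If baseline pain and function explain a share R² of the rating's variation, the effective sample size is about n/(1 − R²). R² is not in the documents, so a range is assumed:
- R² = 0.01: 1/0.99 = 1.01, a gain of about 1%.
- R² = 0.0625: 1/0.9375 = 1.07, about 7%.
- R² = 0.16: 1/0.84 = 1.19, about 19%.

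The improved rates are also assumed. Power for two proportions (two-sided 0.05, pooled variance under the null) is:

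| Improved, control vs Better Hip | BMI only (n = 90) | R² 0.01 | R² 0.0625 | R² 0.16 |
|---|---|---|---|---|
| 25% vs 45% | 80.8% | 81.2% | 83.3% | 87.2% |
| 30% vs 45% | 54.8% | 55.2% | 57.5% | 62.2% |

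**4. Simulation.** 212 randomised, 15% random dropout, 1,500 trials per setting. Logistic models without random effects were fitted with BMI only, and with BMI plus two baseline scores correlated 0.5 (assumed). Relative efficiency refers to the standardised risk difference, and power to the Wald test of the treatment coefficient.

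| Assumed association with baseline | Relative efficiency | Power, BMI only | Power, adjusted |
|---|---|---|---|
| None | 0.99 | 80.8% | 80.8% |
| Weak | 1.01 | 76.6% | 77.1% |
| Moderate | 1.09 | 71.8% | 75.5% |
| Strong | 1.18 | 63.1% | 72.3% |

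The largest gain is 72.3 − 63.1 = 9.2 points. With no treatment effect and a moderate association, both models rejected in 4.9% of trials.

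**5. If the rating reflects only the current state.** A separate simulation used 90 per arm, the plan's correlations of 0.25 and 0.4, and an assumed pain–function correlation of 0.5. The ratio of adjusted to unadjusted variance was 0.996, 0.970, 0.955 and 0.953 as pain and function drove 30%, 50%, 70% and 100% of the rating. The variance falls by 0% to 5%, and power rises by at most 3 points.

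**6. Dropout related to severity.** With moderate association and dropout depending on baseline severity in opposite directions in the two arms (an assumed pattern), the BMI-only risk difference averaged 0.198 against a true 0.176, and the adjusted one 0.175. With weak association the figures were 0.196 and 0.184 against a true 0.184. With no true effect (moderate association) the BMI-only estimate averaged 0.019 and type I error was 5.7%, within simulation error of 5% (standard error about 0.6 points). When dropout depended on severity in the same direction in both arms, the BMI-only estimate stayed close to the truth (0.176 against 0.176).

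**The case against.** The strongest reply is that nothing here is an error. The rule foresees outcomes with no baseline value, no other text contradicts it, and the model includes the stratification factor. A statistical analysis plan is to be written while the biostatisticians are blinded, and it could name further covariates. Effectiveness will be judged on the primary outcomes at 6 months, so no main conclusion depends on this model. All of this stands, and it is why the severity is low. What remains is that the article does state a covariate set, and that set can be improved at almost no cost.

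A reader might infer more than the documents support:

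- **That baseline data are thrown away.** Both scores are used in their own primary models. They are absent from this model only.
- **That the BMI-only comparison is biased by chance imbalance.** Under randomisation, chance imbalance is already reflected in the standard error. The shift in step 6 needs a dropout pattern for which the documents give no evidence.
- **That the planning correlations show a strong link.** The protocol assumes "correlations between baseline and 6-month scores of 0.25 for pain and 0.4 for function". With equal SDs, the correlation of baseline with change is −√((1 − r)/2): −0.61 for pain and −0.55 for function. These describe an arithmetical score change, not a participant's rating, and they need equal SDs. Entry requires walking pain of at least 4, which may narrow the baseline spread. If the baseline SD were 0.75 of the follow-up SD (assumed), pain gives (0.25 − 0.75)/√(0.5625 + 1 − 0.375) = −0.46.
- **That variance would fall by 22% and power rise by 10 points.** Those values arise only if change in pain and function determines the rating completely. At a 30% share the same calculation gives about 4% and 1 point.

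The simulations also omit the participant and physiotherapist random effects, so they indicate order of magnitude only.

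**Conclusion.** The point holds as a low-severity improvement to a secondary analysis. As written, global change is adjusted for BMI stratum alone. That analysis is valid and holds its type I error, but it forgoes available precision. The gain from adding baseline walking pain and WOMAC function is roughly 0% to 19% in effective sample size, about 0 to 9 points of power, and at most about 5% in variance if the rating reflects only the current state. These ranges rest on assumed improved rates and assumed associations, since the documents give neither. When there was no association, adjustment cost essentially nothing (relative efficiency 0.99). The added robustness to dropout matters only if dropout depends on baseline severity differently in the two arms. The documents do not support calling the model invalid or contradictory.

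**What to change.** Add to the binary-outcome part of the Data analysis plan, or to the statistical analysis plan before unblinding:

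> For global change, which has no baseline value, the model is adjusted for baseline walking pain (NRS) and baseline WOMAC function in addition to BMI stratum. Risk ratios and risk differences are obtained by standardising over these covariates.

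Standardising over all randomised participants, as the adjusted model in the dropout simulation did, keeps the estimate tied to the randomised groups when some ratings are missing.

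The cost is one sentence. No new data are needed, and nothing changes for participants. Fixing the covariates in advance also avoids choosing them after the results are seen. Hip replacement likewise has no baseline value, so the authors may wish to confirm that BMI stratum alone is intended there. The documents give no expected number of procedures from which to judge whether that model could carry more covariates.
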